**Primary Safety Endpoints:**

- Serious Adverse Events
- Adverse Events
- Respiratory failure (Hypercapnic)

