**Primary Efficacy Endpoint:**

The Odds of Ratio for Improvement on a 7-point Ordinal Scale on Day 15 [Time Frame: Day 15 from the day of study inclusion]. The odds ratio represents the odds of improvement in the ordinal scale between the treatment groups. The ordinal scale is an assessment of the clinical status at a given day. Each day, the worst score from the previous day will be recorded.

The scale is as follows: 1. Death 2. Hospitalized, on invasive mechanical ventilation or Extracorporeal Membrane Oxygenation (ECMO) 3. Hospitalized, on non-invasive ventilation or high flow oxygen devices 4. Hospitalized, requiring low flow supplemental oxygen 5. Hospitalized, not requiring supplemental oxygen - requiring ongoing medical care (Coronavirus (COVID-19) related or otherwise) 6. Hospitalized, not requiring supplemental oxygen - no longer required ongoing medical care (other than per protocol ZingiVir-H administration) 7. Discharge from hospital.

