**Criteria for Discontinuation from Study Drug or Study Participation**

**Withdrawal from receiving study drug**

A subject may remain in the study but discontinue the administration of study drug at any time during treatment. Reasons for this may include:

- Intolerable adverse event(s)
- Subject’s request
- Investigator’s judgment (e.g. related SAE)
- Administration of study drug is contraindicated if the co-administration of standard of care medication which is required for subject treatment.
- Need for mechanical intubation due to respiratory failure (Hypecapnic)

In any above case of withdrawal or lost to follow-up on the patients status shall be document as appropriate in the patient source document and needs to be reported as appropriate to sponsors.

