**Laboratory Samples**

Hospital laboratory can be used to access the following test. If the hospital laboratory has limitation an outside laboratory with NABL accreditations shall be arranged for sample analysis.

- Complete Blood Count with differential (Hemoglobin, Hematocrit, and WBC with differential count) & ESR – **Day-01, 06, EOT (Day15) & 30 of study period**
- Serum Chemistry- Creatinine, Urea, CRP, ALT, AST, Alkaline Phosphatase, Albumin, total bilirubin- **Day-01, Day 06 Only CRP, End of treatment- Day 10 OR Day 15, & End of study period Day 30**.
- Pregnancy test; Serum or Urine human Chorionic Gonadotropin (hCG) - Pregnancy test only required for woman of childbearing potential on the day of randomization (**Day-01**).
- Immunomodulatory markers, IL6, IL7, Interferon α, IgG, IgM- **Day 01, Day 06, End of treatment- Day 10 OR Day 15, & End of study period Day 30**.

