**Dosing Visits - Day-1 to EOT (Day15)**

The first dose of study drug must be swallowed within 4 hours from the time study inclusion. The study drug shall be continuing daily each consumed once in 3 hours ±1 hour between 6 AM and 9 PM in a given day (6AM, 9AM, 12Noon, 3PM, 6PM, 9PM) for a minimum duration of 10 days to Maximum 15 days whereas the daily dose shall be administered orally once in 4 ±2 hours interval ie 6 tablets per day.

Following the administration of the first dose record the following:

- Changes in concomitant medications
- Adverse Events/Serious Adverse Events
- Major respiratory failure Events
- Interventions or Surgeries
- Vital signs

**Routine assessment visit and Study drug compliance** – Day 2 to EOT (Day 15)

Following assessments must be made on daily basis for each study subject:

- Vital signs: Pulse – Body temperature, beats per minute (BPM), Blood Pressure (BP) mmHg, Respirations – breaths per minute
- Concomitant medications (including medications, fluids and blood products administered within the 7 days prior to randomization).
- Documentation of any adverse events
- Blood will be obtained for following laboratory tests – only on **Day 06**
  - Complete Blood Count with differential (Hemoglobin, Hematocrit, and WBC with differential count)
  - Serum Chemistry ESR, CRP
  - Immunomodulatory markers, IL6, IL7, Interferon α, IgG, IgM

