**Serious Adverse Events**

Information about all serious adverse events (SAEs) will be collected and recorded on the SAE Report form within 24 hours of learning of its occurrence. A paper SAE form should be completed by the site and faxed or emailed to the sponsor within 24 hours using the safety reporting contact information provided. The site is to follow their local regulations related to the reporting of SAEs to their local IRB/IEC. An SAE is any undesirable sign, symptom, or medical condition which:

• Is fatal or life-threatening (i.e. an event with an outcome of ‘Death’), or

• Requires or prolongs inpatient hospitalization, or

• Results in persistent or significant disability/incapacity, or

• Constitutes a congenital anomaly or a birth defect; or

• Is medically significant, as determined by a qualified health professional, may jeopardize the subject, and may require medical or surgical intervention to prevent one of the outcomes listed above

• Major respiratory failure as per ICD-10

• Any adverse event causing the need for unblinding will be handled as a serious adverse event.

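### One of the three primary safety endpoints is limited to hypercapnic respiratory failure, which does not match the events the protocol collects and has no scheduled carbon dioxide measurement behind it

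*Protocol*

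**What the plan says.** The Protocol synopsis, under Primary Safety Endpoints, has three items. The first is "Serious Adverse Events", the second is adverse events, and the third is "Respiratory failure (Hypercapnic". The third has no definition, carbon dioxide threshold or time frame.

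Respiratory failure is mentioned in three other places:

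- Withdrawal from receiving study drug gives as one possible reason: "Need for mechanical intubation due to respiratory failure (Hypecapnic".
- Dosing Visits tells sites, after the first dose, to record "Major respiratory failure Events".
- Serious Adverse Events includes in its definition: "Major respiratory failure as per ICD-10". No codes are listed.

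The chemistry panel under Laboratory Samples is "Creatinine, Urea, CRP, ALT, AST, Alkaline Phosphatase, Albumin, total bilirubin". The other scheduled tests are blood count with ESR, a pregnancy test and immune markers. The daily observations are "Vital signs: Pulse – Body temperature, beats per minute (BPM), Blood Pressure (BP) mmHg, Respirations – breaths per minute".

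**The concern.** An endpoint has to match what is collected, and the planned data must be able to decide whether a patient has had it. The respiratory item does neither well. Sites collect major respiratory failure of any kind, while the endpoint counts only the hypercapnic kind. Nothing scheduled shows which kind an event was.

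The restriction also sits oddly with the rest of the protocol, which follows oxygenation. Entry requires oxygen saturation above 94% on room air and radiographic infiltrates. Ordinal scores 2 to 4 are levels of oxygen or ventilatory support; score 3, for example, is "Hospitalized, on non-invasive ventilation or high flow oxygen devices". The secondary objectives include oxygen saturation, duration of oxygen therapy and need for mechanical ventilation.

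What is at stake is how the safety results are read. This is the only organ-specific primary safety endpoint. A patient whose oxygenation fails would not be counted in the line labelled respiratory failure, and a low figure there could be taken as reassurance that it cannot give.

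**Working it through.** The protocol states no rate of respiratory failure and no hypercapnic share, so there is no figure to reproduce and no arithmetic to do. The check sets every mention of respiratory failure beside every planned measurement.

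**Step 1. Scope of each mention**

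| Protocol section | Use | Limited to hypercapnic? |
|---|---|---|
| Primary Safety Endpoints | Endpoint | Yes |
| Withdrawal from receiving study drug | Reason to stop study drug | Yes |
| Dosing Visits | Event to record | No, but must be major |
| Serious Adverse Events | Part of the definition | No, but must be major |

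The protocol is split two against two. The endpoint and the stopping rule are narrow; the two sections that generate the data are wide. The qualifier also differs: the endpoint specifies a type but no severity, while the collection sections specify a severity but no type.

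**Step 2. Can an event be classed as hypercapnic?** Hypercapnia is raised carbon dioxide, so a carbon dioxide measurement is needed.

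- Laboratory Samples: blood count, ESR, chemistry, pregnancy test and immune markers. No blood gas.
- Day 01, Day 06, end of treatment and Day 30: subsets of the same list. No blood gas.
- Vital signs: pulse, temperature, blood pressure and respirations. No capnography.

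No planned item measures carbon dioxide. Classification would depend on blood gases that happened to be taken in routine care, or on the site's diagnosis.

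**Step 3. Where would failure of oxygenation appear?**

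- In the serious adverse event endpoint, if the event is major, through the ICD-10 item.
- On the ordinal scale, recorded daily from Day 01 to end of treatment and again at end of study, in scores 2 to 4.
- In the secondary objective on need for mechanical ventilation within 30 days, which does not depend on the type of failure.
- Not in the respiratory failure endpoint, unless the event was also hypercapnic and someone recorded it so.

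**Step 4. Can the ordinal scale stand in for the endpoint?** Only as a cross-check. Score 1 is death from any cause, so taking all scores of 3 or lower would mix in deaths that are not respiratory. Scores are also not daily between end of treatment and Day 30. Scores 2 and 3 can be compared with reported events while scoring is daily, and the 30-day ventilation outcome covers part of the later gap.

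**The case against.** The strongest reply is that little is lost. The item is one of three primary safety endpoints, and major respiratory failure of any type already counts under another of them, serious adverse events. Worsening to high-flow oxygen or ventilation is also visible in the primary efficacy endpoint and in the ventilation and oxygen-therapy outcomes. All of this stands. A reader of the endpoint line alone might infer that the primary safety assessment as a whole counts only hypercapnic failure, or that the trial would miss failure of oxygenation. The documents do not support either reading.

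A second reply is that the hypercapnic wording may be deliberate, since it recurs in the withdrawal section, and that an endpoint may be narrower than a category of serious adverse event. That is fair. But if it is deliberate, the protocol still has to say how an event is recognised.

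A third is that respiratory failure is event-driven and can be classified from source records, with any definition left to the analysis plan. That holds in part. Source records may contain a blood gas, and an analysis plan may define terms. It cannot supply a measurement that the visit schedule omits, and nothing in the protocol ensures that one is taken.

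What remains is that serious adverse events pool respiratory failure with every other serious event. The line named respiratory failure would still be narrower than its label suggests.

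**Conclusion.** The inconsistency is real and its effect is limited. One of three primary safety endpoints is restricted to hypercapnic failure, does not match the two sections that collect respiratory failure, and cannot be reliably classified, because none of the scheduled assessments measures carbon dioxide. Followed as written, it would exclude failure of oxygenation from the reported respiratory line, although other outcomes would show it.

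The size cannot be stated as a number of events. A reader might infer that the count would be close to zero in both arms, or that most events would be missed. The protocol gives neither a rate of respiratory failure nor a hypercapnic share, so any such figure would rest on assumption alone. The conclusion needs no rate. It rests on the text of the four sections and on reading the listed assessments as the full schedule.

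This should be corrected before the safety results are tabulated. It does not put the trial's safety reporting as a whole in doubt.

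**What to change.** Under Primary Safety Endpoints, restate the third item as major respiratory failure of any type, as already collected under Dosing Visits and Serious Adverse Events. State the ICD-10 codes that qualify and the time frame.

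Cross-check reported events against ordinal scores 2 and 3, daily to end of treatment and at end of study, and against the 30-day mechanical ventilation outcome. Query any disagreement; do not use the scores as the definition. Report hypercapnic failure as a subset where a blood gas exists, with the number of events that had one.

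If the sponsor does intend a hypercapnic-only endpoint, the protocol must give its definition and the source of the carbon dioxide data.

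The withdrawal section uses the hypercapnic wording in a rule for stopping study drug. The sponsor must reconcile it with the other three sections; no view is taken here on which clinical rule is right.

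The cost is a wording amendment and a short code list, using events and scores already collected. The small downside is that the item becomes a named subset of the serious adverse event endpoint, so the two are not independent and should not be added together.

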**Statistical Methods:**

The total sample size is 112 randomized subjects. This sample size is allocated to treatment arms in a 1 to 1 ratio. This sample size provides 50% power if the following assumptions are made based on earlier reviews. SAS 9.4 statistical analysis software will be used for statistical analyses. T-test will be used for comparisons between groups for continuous variables. The comparison between groups for categorical variables will be performed using Fisher's exact probability method. Means and standard deviations will be used to describe centralized discrete trends. The t-test, rank-sum test, and Fisher's exact probability method will be used for comparisons between groups. P 0.05 indicates that the difference was statistically significant.

**RANDOMIZED CONTROLLED SINGLE BLINDED PROSPECTIVE MULTI CENTRE CLINICAL TRIAL TO INVESTIGATE THE SAFETY AND EFFICACY OF ZINGIVIR-H AS AN ADJUVANT THERAPY IN HOSPITALIZED ADULTS DIAGNOSED WITH CORONAVIRUS DISEASE 2019 (COVID-19).**

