**Secondary Efficacy Endpoint:**

- Proportion of Participants experiencing Treatment-Emergent Adverse Events [Time Frame: First dose date up to 15 days]
- Changes in Haematological and Biochemical parameter like CBC,ESR, CRP, Troponin, Liver function test, Renal function test, [Time Frame: First dose date up to 15 days]
- Changes in inflammatory markers - IL2, IL6, Interferon α, IgG, IgM
- Significant changes in the Chest X-Ray before and after treatment.

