**Visit Schedule and Assessments**

**Screening / Randomization Visit – Day 01**

Subjects must meet the inclusion criteria and have none of the exclusion criteria in order to be eligible for randomization in this study. Subjects who meet all eligibility criteria, and have signed informed consent will be discussed randomize and move on to the Baseline study visit. Once the subject is randomized the sponsor representative or the study Investigator will provide the study staff with a unique randomization number for the subject.

Following assessments must be made at this Baseline visit for each study subject:

- RT-PCR test assuring the subjects test positive for COVID-19.
- Demographics
- Medical history (all known information regarding the subject’s health history/relevant surgeries/interventions prior to signing the informed consent).
- Vital signs: Body temperature, Pulse – beats per minute (BPM), Blood Pressure (BP) mmHg, Respirations – breaths per
- Concomitant medications (including medications, fluids and blood products administered within the 7 days prior to randomization).
- Documentation of any other infection if available (site of infection and, if available: positive culture results, prior antibiotics, sensitivity of cultured organism to antibiotics, nonmedical treatment such as surgery or drainage).
- Physical Examination including the following: general appearance, Head, Eye, Ear Nose Throat (HEENT), neck, respiratory, cardiovascular, chest, abdomen, lymphatic, musculoskeletal and extremities, skin and neurologic examination. Height and weight (baseline dry weight).
- Blood will be obtained for following laboratory tests:
  - Complete Blood Count with differential (Hemoglobin, Hematocrit, and WBC with differential count) & ESR
  - Serum Chemistry- Creatinine, Urea, CRP, ALT, AST, Alkaline Phosphatase, Albumin, total bilirubin
  - Pregnancy test; Serum or Urine human Chorionic Gonadotropin (hCG) - Pregnancy test only required for woman of childbearing potential on the day of randomization
  - Immunomodulatory markers, IL6, IL7, Interferon α, IgG, IgM

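### Laboratory changes are assigned an unadjusted t-test, the rank-sum test has no stated role, and the Day 01 value is not used as a covariate

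*Protocol*

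**What the plan says.** The Statistical Methods section of the protocol synopsis fixes the comparison: "T-test will be used for comparisons between groups for continuous variables". Description is also fixed: "Means and standard deviations will be used to describe centralized discrete trends". A further sentence adds a third method without attaching it to any variable: "The t-test, rank-sum test, and Fisher's exact probability method will be used for comparisons between groups". The section names no covariate, transformation or regression model.

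The Secondary Efficacy Endpoint section makes laboratory changes into endpoints: "Changes in Haematological and Biochemical parameter like CBC,ESR, CRP, Troponin, Liver function test, Renal function test", with a time frame up to 15 days, and "Changes in inflammatory markers - IL2, IL6, Interferon α, IgG, IgM", with no time frame.

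The baseline value is planned. The Day 01 visit takes blood for blood count, ESR, a chemistry panel that includes CRP, and "Immunomodulatory markers, IL6, IL7, Interferon α, IgG, IgM". The Laboratory Samples section repeats these at end of treatment and Day 30, with some of them on Day 06.

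**The concern.** Markers such as CRP and IL6 are positive and can be strongly right-skewed. In a raw change score a few very high values then dominate the mean and the SD, and a t-test on that change is inefficient. Subtracting the baseline is also not the most efficient way to use it: unless baseline and follow-up are almost perfectly correlated, a change score carries avoidable noise that a covariate would remove.

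The rank-sum test would be less sensitive to outliers, but with no rule for when it applies, the choice between the two tests can be made after the data are seen. At stake is the precision of the secondary laboratory comparisons and some freedom in which p-value is reported. The primary endpoint, the Day 15 ordinal odds ratio, is not touched.

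**Working it through.** **Inputs from the protocol.** "The total sample size is 112 randomized subjects", allocated 1:1, with 10% drop-out and 100 evaluable. Check: 100 / (1 − 0.10) = 111.1, rounded up to 112, which reproduces. That leaves 50 evaluable per arm. The significance level is 0.05; two-sided is assumed, because the protocol does not say.

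**Inputs not in the protocol (assumed).** Log-normal marker with equal log-SD at both times; correlation r between Day 01 and follow-up on the log scale; a true 40% reduction, so the log effect is ln 0.6 = −0.511.

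**Step 1: the covariate alone, no skew.** The SD of a change score is σ√(2(1 − r)). The residual SD under ANCOVA is σ√(1 − r²). The variance ratio is (1 − r²) / (2(1 − r)) = (1 + r)/2. If the t-test on change has 80% power, ANCOVA has Φ(2.802/√((1 + r)/2) − 1.960). For r = 0.5: 2.802/0.866 − 1.960 = 1.275, giving 89.9%. Likewise 93.5% for r = 0.3, 86.0% for r = 0.7 and 82.0% for r = 0.9. The gain from the covariate alone is therefore 2 to 14 points.

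**Step 2: adding skew.** On the log scale the normal approximation can be done by hand. At log-SD 1.0 and r = 0.5:

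- t-test on log change: SE = 1.0 × √(2 × 0.5) × √(2/50) = 0.200; 0.511/0.200 − 1.960 = 0.594; power about 72%.
- ANCOVA on log values: SE = 0.866 × 0.200 = 0.173; 0.511/0.1732 − 1.960 = 0.99; power about 84%.

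The raw-scale tests need simulation (50 per arm, r = 0.5, 40% reduction, thousands of trials per setting). Approximate power:

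| log-SD | t-test, raw change | rank-sum, raw change | ANCOVA, log scale |
|---|---|---|---|
| 0.5 | 98% | 99% | 100% |
| 0.8 | 59% | 73% | 95% |
| 1.0 | 36% | 53% | 82% |
| 1.5 | 13% | 26% | 49% |

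**Step 3: where the gain comes from.** At log-SD 1.0 the simulated t-test on log change has 71%. The log scale supplies 71 − 36 = 35 points and the covariate 82 − 71 = 11.

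**Step 4: validity.** With no treatment effect, the t-test on raw change rejected in about 3% to 5% of simulated trials, so it is not anticonservative. Reporting whichever of the t-test and the rank-sum test is significant rejected in about 6% to 8%.

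**Step 5: can the fix be run?** The endpoint list contains IL2 and troponin. The laboratory lists (Laboratory Samples and each visit) contain neither; they have IL6 and IL7, and a chemistry panel without troponin. A Day 01 covariate therefore exists on schedule for most endpoint markers, but not for these two.

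**The case against.** The strongest reply has four parts.

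First, a reader might infer that the plan ignores the Day 01 value. It does not: the endpoints are changes, and a change uses Day 01 by subtraction. Only the covariate adjustment is missing.

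Second, a reader might infer that skewed markers will certainly go to the t-test. The rank-sum test is also listed, and against it the loss at log-SD 1.0 is 82 − 53 = 29 points rather than 82 − 36 = 46. This is a fair correction. Some loss remains, and the role of the rank-sum test is still unassigned.

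Third, a reader might infer a large loss of power for every marker. The documents give no SD, skew, correlation or effect for any of them. At log-SD 0.5 with the assumed effect the methods barely differ, and nothing suggests that a log scale is needed for haemoglobin or albumin. The stated 50% power cannot be used to argue urgency either, because the protocol ties it to no marker and omits its assumptions.

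Fourth, covariates and transformations are often left to a statistical analysis plan, which may exist. That would answer a complaint about missing detail. Here, however, the protocol names a test for continuous variables, and a more efficient one is available from data it already schedules.

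**Conclusion.** The point holds as an efficiency issue on secondary endpoints. The protocol assigns an unadjusted t-test with means and SDs to continuous variables, leaves the rank-sum test without a role, and does not use Day 01 as a covariate where it is scheduled. The cost ranges from about 2 power points at log-SD 0.5 to about 46 at log-SD 1.0 against the t-test, and from 1 to 29 against the rank-sum test. These figures assume 50 per arm, a 40% reduction, r = 0.5 and a log-normal marker. Most of the gain comes from the log scale. A single prespecified t-test does not inflate type I error, so the validity of the trial is not in question. Severity is low.

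**What to change.** For each marker with a scheduled Day 01 value, compare the arms at end of treatment (Day 15 time frame) by ANCOVA of the follow-up value on treatment and the Day 01 value.

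- Name in advance the markers treated as right-skewed (for example CRP and IL6). Analyse these on the log scale and report a ratio of geometric means with a 95% CI.
- Keep the untransformed scale for the others (for example haemoglobin and albumin).
- Make the rank-sum test a named sensitivity analysis.
- State which sample is the follow-up value, because the Laboratory Samples section allows end of treatment to fall on Day 10 or Day 15 for chemistry and immune markers.
- Reconcile the endpoint list with the laboratory lists for IL2 and troponin before applying the method to them.

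The cost is a few sentences and routine SAS code, with no new samples for markers already scheduled. The downside is that log analysis needs a prespecified substitution rule for values below the detection limit.

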**Secondary:**

- Time to a normal body temperature [ Time Frame: From the time of randomization until the time of normal body temperature, assessed up to 15 days]
- Time to the alleviation of nasal/throat/chest symptoms [ Time Frame: From the time of randomization until the time of absence of nasal/throat/chest symptoms, assessed up to 15 days
- Proportion of participants in each group with normalization of fever [ Time Frame: day 7 and day 15 ]
- Proportion of participants in each group with oxygen saturation > 94% on room air for >24h [ Time Frame: day 7 and day 15 ]
- Time to fever normalization (if febrile at baseline) [ Time Frame: within 15 days ]
- Time to first negative SARS-CoV-2 PCR in NP swap (if pos. at baseline) [ Time Frame: within 15 days ]
- Time to first negative SARS-CoV-2 PCR in lower respiratory tract specimens (sputum, bronchoalveolar lavage, tracheal aspirate) (if positive at baseline) [ Time Frame: within 15 days ]
- Duration of oxygen therapy [ Time Frame: within 30 days ]
- Proportion of participants in each group with need for mechanical ventilation [ Time Frame: within 30 days ]
- Duration of hospitalization [ Time Frame: within 28 days ]
- All cause mortality [ Time Frame: day 30 ]

**Study Center(s):** Study in Indian population and recruitment will happen up to 5 research sites based on competitive patient recruitment.

**Phase of Development:** Proof of Concept/ Intervention Trial on traditional medical product.

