**Study Period:**

Estimated time of first subject enrollment: 1 Q 2020

Estimated time of last subject enrollment: 1Q 2020

Number of Subjects (planned): Approximately 112 randomized subjects with assumed drop-outs of 10%; 100 evaluable subjects.

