**INVESTIGATIONAL PLAN**

**Overall Study Design**

This is a Randomized controlled, single blinded multi-center, comparative study of ZingiVir-H as an adjuvant therapy in hospitalized adults diagnosed with coronavirus disease 2019 (COVID-19). At inclusion, subjects who meet all inclusion criteria and no exclusion criteria will be assigned, in either therapeutic arm (ZingiVir-H), to receive ZingiVir-H in a dose of 500 mg tablet each consumed once in 3 hours ±1 hour between 6 AM and 9 PM in a given day (6AM, 9AM, 12Noon, 3PM, 6PM, 9PM) for a minimum duration of 10 days to Maximum 15 days OR will be on a Placebo arm to receive placebo (without active ingredients) each consumed once in 3 hours ±1 hour between 6 AM and 9 PM in a given day (6AM, 9AM, 12Noon, 3PM, 6PM, 9PM) for a minimum duration of 10 days to Maximum 15 days. The allocation of study arm is strictly as per the discretion of the Investigator. Whereas both the study groups shall be given standard of care of treatment as per the research site policies or COVID-19 therapeutic management policies. These doses will be administered orally. Blood samples for assessing CBC; safety laboratory tests and immunomodulatory markers will be obtained between baseline assessments (Day-01), during the day-06 of inclusion, at the end of the treatment day-15 and at the end of the study day-30. Safety-related assessments will include reports of adverse events and clinical laboratory test results.

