**Ordinal Scale assessment: Day 01 to EOT & EOS**

Ordinal Scale on the Odds of Ratio of Improvement on a 7-point scale between the treatment groups. The ordinal scale is an assessment of the clinical status will be assessed and documented on daily basis from Day-01 to EOT and on EOS. Each day, the worst score from the previous day will be recorded in the CRF.

The scale is as follows: 1. Death 2. Hospitalized, on invasive mechanical ventilation or Extracorporeal Membrane Oxygenation (ECMO) 3. Hospitalized, on non-invasive ventilation or high flow oxygen devices 4. Hospitalized, requiring low flow supplemental oxygen 5. Hospitalized, not requiring supplemental oxygen - requiring ongoing medical care (Coronavirus (COVID-19) related or otherwise) 6. Hospitalized, not requiring supplemental oxygen - no longer required ongoing medical care (other than per protocol ZingiVir-H administration) 7. Discharge from hospital.

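### The protocol names only unadjusted two-group tests although site, age and Day 01 CRP are recorded, so the Day 15 ordinal comparison may give up some power that adjustment would recover

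*Protocol*

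**What the plan says.** The protocol's only statistical text is the Statistical Methods paragraph of the synopsis. For categorical outcomes it says "The comparison between groups for categorical variables will be performed using Fisher"'s exact method; it then lists the t-test, the rank-sum test and Fisher's test for between-group comparisons in general. It names no model, covariate or stratum.

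The Primary Efficacy Endpoint is an odds ratio for improvement on a 7-point scale at Day 15. The Statistical Methods paragraph does not say which listed test serves it, and no cut-point for a 2x2 table is given.

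On size, the same paragraph states "The total sample size is 112 randomized subjects", "This sample size is allocated to treatment arms in a 1 to 1 ratio" and "This sample size provides 50% power if the following assumptions are made based on earlier reviews". No assumptions follow that last sentence. The Study Period section adds "Approximately 112 randomized subjects with assumed drop-outs of 10%; 100 evaluable subjects".

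On sites, the Study Center(s) entry says "recruitment will happen up to 5 research sites based on competitive patient recruitment". Overall Study Design says "both the study groups shall be given standard of care of treatment as per the research site policies", and the sentence goes on to offer general COVID-19 treatment policies as an alternative.

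On data held, the site number is part of the subject number (Data Management, Documentation). Demographics and CRP are taken at the Day 01 visit. The ordinal scale "will be assessed and documented on daily basis from Day-01 to EOT and on EOS".

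**The concern.** The top three categories of the scale separate patients by whether ongoing care is judged necessary and whether they have gone home. Entry requires hospitalisation, need for care and oxygen saturation above 94% on room air, so nearly all patients should start in category 5. Much of the Day 15 variation is then likely to lie in categories 5 to 7. The protocol sets no common discharge rule, and standard of care may differ by site, so Day 15 scores may differ by site for reasons unrelated to treatment.

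An unadjusted test leaves such differences, and the prognostic spread from age and CRP, in its error. In a trial that states only 50% power, even a few points are worth having when the variables are already collected. The Day 01 ordinal score would add little, because it hardly varies at entry. The candidates are therefore site, age and Day 01 CRP.

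**Working it through.** **1. The plan's own figures.** 100/(1 - 0.10) = 111.1, which rounds up to the stated 112: 56 per arm randomised, about 50 evaluable. The 50% power cannot be reproduced because its assumptions are absent. Taking two-sided 0.05 (sidedness is not stated), 50% power corresponds to a standardised difference of 1.96 x sqrt(2/n): 0.39 for n = 50 and 0.37 for n = 56. With 50 per arm and assumed control improvement rates of 40% to 80%, that is an odds ratio of about 2.2 to 3.5.

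**2. Baseline covariates, by formula.** If the covariates have correlation rho with the outcome, the error variance falls by the factor 1 - rho². Starting from 50%, power = Phi(1.96/sqrt(1 - rho²) - 1.96).

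| rho (assumed) | 1.96/sqrt(1 - rho²) | Power |
|---|---|---|
| 0.2 | 2.000 | 51.6% |
| 0.3 | 2.055 | 53.8% |
| 0.35 | 2.092 | 55.3% |
| 0.5 | 2.263 | 61.9% |

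The gain is about 2 to 5 points for rho of 0.2 to 0.35. The formula charges nothing for estimating the extra terms.

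**3. Site, age and CRP together, by simulation.** N = 100 and 5 sites. Assumed site SD on the logit scale, and effects of age and CRP per SD: weak 0.4, 0.3, 0.3; moderate 0.7, 0.5, 0.5; strong 1.0, 0.7, 0.8.

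| Prognostic strength | Ordinal, OR 2.2: rank test, unadjusted to adjusted | Binary, OR 2.5: logistic, unadjusted to adjusted |
|---|---|---|
| None | 45% to 43% | 55% to 55% |
| Weak | 42% to 42% | 50% to 53% |
| Moderate | 37% to 40% | 44% to 49% |
| Strong | 30% to 38% | 37% to 47% |

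The binary gains are a little generous: the adjusted likelihood-ratio test rejected 5.7% to 6.2% of the time under the null.

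**4. Site alone, by simulation.** 100 patients, 5 equal sites, Day 15 discharge as a binary outcome, arms balanced within site. CMH is the site-stratified Cochran-Mantel-Haenszel test.

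| Control rates across sites (assumed) | OR | Fisher | Chi-square | CMH | CMH minus chi-square |
|---|---|---|---|---|---|
| Identical | 2.5 | 53% | 61% | 61% | 0 |
| 40-60% | 2.5 | not run | 60.1% | 60.3% | 0.2 |
| 30-70% | 2.5 | 48% | 56% | 58% | 2 |
| 20-80% | 2.5 | 38% | 47% | 54% | 7 |
| 10-90% | 3 | 35% | 44% | 58% | 14 |

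The 40-60% row comes from a series of 20,000 runs; the others used 4,000 (Monte Carlo error about 0.8 points). The longer series gives 45.9% against 52.0% at 20-80%, a gain of 6 points; at 10-90% repeat runs put the gain at 13 to 14.

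The protocol does not say that randomisation is stratified by site. If only the overall 1:1 split is fixed, the gains shrink: identical sites 61% to 59% (a loss of 2), 20-80% 46% to 51% (a gain of 5), 10-90% 46% to 57% (a gain of 11).

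**5. What belongs to Fisher's test itself.** With identical sites, Fisher trails chi-square by 61 - 53 = 8 points; in the other rows the gap is 8 or 9. This is the exact test's conservatism, not lost site or covariate information.

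**6. Null behaviour.** With arms balanced within site and control rates spread 30-70% or wider, the unadjusted tests fall below 5%: about 1 to 2% for Fisher and 2 to 4% for chi-square. CMH stayed at 5.0 to 5.8%. The conservatism of chi-square here depends on the within-site balance.

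**The case against.** The strongest reply is that covariates, strata and pooling of small sites are ordinary statistical analysis plan content, that a synopsis paragraph excludes none of them, and that under randomisation an unadjusted test is valid, with chance imbalance already covered by its error rate. The validity point stands: this is about efficiency. The scope point stands only in part, because the protocol does not leave the method open. It names a list of tests, all unadjusted, and a later adjusted primary analysis would depart from that list.

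Three stronger readings are tempting, and the protocol does not support them.

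- A reader might infer that Fisher's test is the fixed primary analysis. The sentence is a general rule for categorical variables, the rank-sum test is also listed, and no test is tied to the Day 15 endpoint.
- A reader might infer that discharge follows each site's own policy. The text on site policies concerns standard of care, and it offers general COVID-19 policies as an alternative. Site-driven discharge is an inference from the lack of a common rule, and there may be fewer than five sites.
- A reader might infer a definite loss of 5 to 10 points, or more against Fisher. Section 4 of the working shows 2 points or less up to a 30-70% spread; larger gains need a wide spread. In the ordinal simulation, the form closest to the endpoint, only the strong case exceeds 5 points. Of the gap to Fisher, 8 to 9 points have another cause.

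It is also fair that entry limits of age 18 to 60 and saturation above 94% narrow the prognostic range, so age and CRP may predict weakly.

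**Conclusion.** The point holds in a limited form. The protocol names only unadjusted tests while holding site, age and Day 01 CRP, so it may give up some power. The amount is unknown, because no site rates, correlations or power assumptions are given. It may be negligible if sites are alike and the covariates predict weakly, is a few points under moderate assumptions, and reaches 13 to 14 points only with very wide site differences and arms balanced within site. The site figures also treat the ordinal outcome as binary.

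The case for acting rests on the asymmetry: a cost of up to about 2 points if the adjusters carry no information, against a gain that grows with their prognostic strength, at no cost in data. Adjustment repairs neither the missing assumptions behind the 50% power nor the statement in Overall Study Design that allocation is at the investigator's discretion. Both are separate and weightier matters.

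**What to change.** In Statistical Methods, tie a named analysis to the Day 15 endpoint: the treatment odds ratio from an ordinal model adjusted for site, age and Day 01 CRP. State in advance, before unblinding, how sites with few patients are pooled and in what form age and CRP enter. If a rank or 2x2 test is preferred, stratify it by site (van Elteren or Cochran-Mantel-Haenszel). Keep the unadjusted comparison as a sensitivity analysis.

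This needs wording only: no new patients, visits or assays. The costs are up to about 2 points of power if the adjusters are not prognostic, and an odds ratio that is conditional on site and covariates and should be reported as such.
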